## Abstract

**Background:**

Inactive and unhealthy lifestyles are common among adolescent men. The planned intervention examines the effectiveness of an interactive, gamified activation method, based on tailored health information, peer networks and participation, on physical activity, health and wellbeing in young men. We hypothesize that following the intervention the physical activation group will have an improved physical activity, as well as self-determined and measured health compared with the controls.

**Methods/design:**

Conscription-aged men (18 years) attending compulsory annual call-ups for military service in the city of Oulu in Finland (n = 1500) will be randomized to a 6-months intervention (n = 640) or a control group (n = 640) during the fall 2013. A questionnaire on health, health behaviour, diet and wellbeing is administered in the beginning and end of the intervention. In addition, anthropometric measures (height, weight and waist circumference), body composition, grip strength, heart rate variability and aerobic fitness will be measured. The activation group utilizes an online gamified activation method in combination with communal youth services, objective physical activity measurement, social networking, tailored health information and exercise programs according to baseline activity level and the readiness of changes of each individual. Daily physical activity of the participants is monitored in both the activation and control groups. The activation service rewards improvements in physical activity or reductions in sedentary behaviour. The performance and completion of the military service of the participants will also be followed.

**Discussion:**

The study will provide new information of physical activity, health and health behaviour of young men. Furthermore, a novel model including methods for increasing physical activity among young people is developed and its effects tested through an intervention. This unique gamified service for activating young men can provide a translational model for community use. It can also be utilized as such or tailored to other selected populations or age groups.

**Trial registration:**

ClinicalTrials.gov Identifier: NCT01376986

## Background

Particularly in industrialised wealthy societies physical inactivity causes 1.9 million deaths per year [1] because of its several adverse health effects [2]. Physical activity provides important health benefits already in adolescence, including reduced symptoms of depression and anxiety, improved physical fitness, as well as reduced body fatness and favourable cardiovascular and metabolic disease risk profiles [3]. Positive health effects of a physically active lifestyle among youth are tracked to adulthood, such as lesser amount of adult obesity [4,5]. Sedentary behaviour and physical activity have also been shown to persist and track from youth into adulthood [5,6]. Despite the known benefits of physical activity on health and future life opportunities, recent evidence consistently demonstrates that a majority of adolescents do not meet current physical activity and public health recommendations of at least 60 minutes per day of moderate or vigorous intensity activity on at least five days per week [3,7,8]. In fact, even less than 10% of the 16–19 years old meet these recommendations [9]. Obesity has become more common while physical fitness has deteriorated markedly. The change in weight has been rapid where the average weight of male adolescents has increased by more than six kilos over a period of 13 years [10]. At the same time, physical performance has declined dramatically [11,12].

Recent evidence underlines the importance of focusing on the balance of light-intensity activities and sedentary behaviours due to the deleterious effects of sitting on health and wellbeing [13]. A meta-analysis showed a dose–response relation between increased sedentary behaviour and unfavourable health outcomes in children and youth [14]. Furthermore, a reduction in any type of sedentary time is associated with lower health risk in youth. Daily TV viewing in excess of 2 hours is associated with diminished physical and psychosocial health, and a lowered sedentary time reduces body mass index [14]. Physical inactivity has also been associated with an increased likelihood of having several emotional and behavioural problems among boys [15-17]. Hence, an early intervention promoting physical activity and decreasing sedentary behaviour at young age may prevent any future adverse health outcomes.

At present it is not known what the most appropriate method for promoting physical activity among young men is. This would require knowledge and understanding of factors related to deciding to engage in or abstain from physical activity. Interventions to promote physical activity have typically involved teaching individuals the skills to change their activity behaviour, providing knowledge about the goals or opportunities of physical activity, or creating a more physically active environment. In adolescents, multicomponent interventions including school, family and communal elements seem to be most beneficial, yet studies outside the school setting are called for [18,19]. Tailored health communication has proved to be an effective method in promoting healthy behaviours [20,21], but has not been utilized in activation interventions among youth. Innovative approaches taking into account the context of changing youth cultures and trajectories are needed.

In research of behaviour and behaviour change understanding and analysing the phenomena in its socio-cultural setting is essential [22]. Qualitative research methods allow observing the phenomena multifaceted and in the actual context [23]. Thus the socially constructing cultural meanings such as values, attitudes and motives, which direct the actual health behaviour, can be incorporated to the study of the physical activity and activation of young men. Both cultural studies of health and technology are recognised fields of research [24,25], but the combination of these in studies which aims at activation of certain populations through intervention are just emerging.

There is indicative evidence that information and communication technologies (ICTs) such as the Internet and mobile phones can be more effective than other methods for carrying out physical activity interventions among young people [26]. The technology allows a possibility to distribute tailored feedback to a wide range of people and settings in a low cost manner [18,27]. One effective way to convey health information and affect health behaviour could be through games [28,29]. Recent RCT trials show successful interventions [30] and improved health-related behaviour [31,32] through the use of games. Recently, a study showed that using a 3D fantasy game for the treatment of depressive symptoms among adolescents was as effective as conventional counselling and significantly reduced depression, anxiety and hopelessness, and improved quality of life [33]. It seems that the inherent orientation towards playing together transfers from other areas of life into computer games. Social skills are needed, or must be developed, in order to succeed in most of the multi-player games. The social bonding can be so strong that it becomes one of the most important motivating factors for playing the games [34]. This might also apply in the context of physical activation when utilizing a game technology. In this study gamification means the process of increasing user engagement and participation by integrating game mechanics into other youth oriented services, such as communal services, networking and distribution of health information [35].

### Objectives

The overall aim of the study is to provide new evidence-based knowledge for promoting health and wellbeing in young men. The purpose is to set up a multidisciplinary approach for assessing the effectiveness of 1) an interactive, gamified activation method, based on peer networks and participation, on physical activity, aerobic fitness and relationship towards physical activity in young men 2) the gamified activation on physical health, with special emphasis on weight and related factors, and on mental and social health and wellbeing.

The hypotheses are that by the end of the intervention the men in the activation group: 1) are physically more active and fit, and 2) their self-determined and measured health is better and there are fewer obese subjects compared to the control group.

## Methods

### Study design

The study design is a parallel-group randomized controlled trial consisting of an intervention and a control group of young men. The protocol has been registered to the clinical trials register (NCT01376986, ClinicalTrials.gov). The study consists of collection of cross-sectional questionnaire and measurement data at the annual call-ups during the fall 2013 followed by a randomized controlled 6-month physical activity intervention. In addition, the subjects’ entry into military service and its course will be followed (Figure 1).

**Figure 1 F1:**
[figure not shown]
**Study design of the population-based randomized controlled trial.** PA = physical activity.

The statement in favour of the study has been received from the Northern Ostrobothnia Hospital District ethical committee (ETTM123/2009). All the involved organisations have provided permission for conducting the study. All subjects will receive both oral and written information and will be requested for a written consent of their participation. The provided information describes the project and its benefits and possible inconvenience or risks to the subjects, as well as their right to refuse or withdraw from the study without any effects on their future health care or military service. The study is conducted according to Declaration of Helsinki. The subjects’ personal data will be protected using number codes. The collected information will only be used by the research group. The transfer and protection of data will be monitored throughout the project, particularly in interactive web-based and mobile device networks.

### Subjects

In Finland military or civil service is mandatory for all male citizens and annually all 18-year old men are called for service in call-ups. Hence, the entire age cohort attends the call ups except those whose physical or mental health or psychological capacities do not allow independent living. In the call-ups fitness for service is determined based on an interview and a prior medical examination conducted less than six months ago. Conscripts are either assigned or exempted from military service, or ordered to attend a new examination at a later call-up.

The total population of eligible participants include all conscription aged men attending the call-ups in the Oulu area (approximately 1500 annually) in northern Finland.

### Sample size

The primary outcome variable is the change in the time spent in physical activity of different intensities (sedentary, light, moderate and vigorous). The aim is to lower the proportion of inactive men by one third in the intervention group with no change in the control group. At baseline, the estimated number of inactive men is 212 (27.6%, data from the 2009 call-ups). With study power of 80% and significance level of 5%, the calculated sample size is [(27.6 × (100–27.6) + 18.5 × (100–18.5)]/[(27.6-18.5)^2^] × 7.9 = 335 persons/group.

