### Setting and randomization

The recruitment is performed at the call-ups for military service in Oulu arranged by the Finnish Defence Forces and City of Oulu every September. Oulu (65°N 25°E) is a growing university town in the northern Finland of approximately 190 000 inhabitants, of which a substantially high proportion are children and adolescents. The unemployment rate of the young people (<25 years) is relatively high in Oulu (19%) compared to other areas in Finland (14%) [36]. Conscription-aged men provide a large, population-based representative sample of young men. All those determined fit for service, who are granted postponement or are exempted from service (n = 1500) will be included in the intervention study. Annually approximately 35% of the conscription aged men in Oulu area are exempted from service, which is the highest proportion in Finland. Adolescents and young men exempted from compulsory military or civil service comprise of a group with a wide range of psychosocial problems and are a target population for supportive interventions [37]. Based on experience for pilot study conducted in 2011, it is estimated that approximately 15% of the men refuse to participate. Thus, approximately 1280 men are expected to participate. These will be randomly allocated into an intervention (n = 640) and control group (n = 640) using computer-generated random numbers. With an estimated 30% dropout rate there will be 447 boys in each group at the end of the intervention.

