#### Main and secondary outcome measures

The main outcome measure is self-determined and objectively measured physical activity. Daily physical activity will be followed using a wrist-worn physical activity monitor, Polar Active (Polar Electro Ltd, Finland) [41-46]. This recorder utilizes frequency and regularity of hand movements adjusted for body parameters and a high agreement with energy expenditure has been observed [46]. The device measures physical activity continuously as metabolic equivalents (MET) per 30 s and as time spent at five different zones (very easy, easy, moderate, vigorous, vigorous+), as well as sleep onset and duration. Self-determined physical activity level will be enquired according to questions widely used in health studies [47].

The type of physical activity (sitting/standing, walking, running, cycling and driving) will be tracked using a smartphone with triaxial accelerometers [48-50]. The recognition is based on different features of the acceleration signal and classification is done using *knn* (k nearest neighbours) and QDA (quadratic discriminant analysis) classifiers. The software has a real-time recognition accuracy of 95% when the phone is in the pocket of the subject’s trousers [50].

The secondary outcome is the proportion of overweight and obese boys.

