### Statistical analysis

Descriptive analyses will be performed utilising the results of the questionnaires and measurements. Absolute and percentage changes from baseline will be calculated for continuous variables. The paired samples t test will be used to compare means of the within group change from baseline, and the t test for independent samples will be used to compare means between the treatment and the control group. The analysis of variance for repeated measures will be used to analyse the intra-group-by-time-effect and the group-by-time interaction and to adjust for possible confounding factors over the study period. The changes in activity and weight during the trial and follow-up will also be examined by multiple linear regression analyses with generalized estimation equations (GEE) to account for correlations between repeated measurements. Association between the response and explanatory factors in the aggregated data will first be analysed using cross tabulation and the Pearson product–moment correlations. Multiple linear and logistic regression analysis using all variables associated with activity level and weight in univariate analyses will be performed to evaluate the determinants of change within the exercise group and the pooled groups. Data will be analysed using both intention to treat and per protocol basis.

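### The 335 per group and 80% power are computed for the proportion of inactive men, not for the stated primary outcome of change in activity time, whose power is unknown

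*Protocol article*

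**What the plan says.** In the protocol article, the Sample size section opens with a continuous outcome: "The primary outcome variable is the change in the time spent in physical activity of different intensities (sedentary, light, moderate and vigorous"). The next sentence moves to a proportion: "The aim is to lower the proportion of inactive men by one third in the intervention group with no change in the control group". The starting rate is given as "At baseline, the estimated number of inactive men is 212 (27.6%, data from the 2009 call-ups"), and the calculation is introduced by "With study power of 80% and significance level of 5"%. It is a two-proportion formula for 27.6% against 18.5% and returns 335 persons per group.

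The section on main and secondary outcome measures describes the main outcome broadly: "The main outcome measure is self-determined and objectively measured physical activity". It then adds: "The secondary outcome is the proportion of overweight and obese boys". It does not list the proportion inactive under either heading, and the article nowhere defines inactive.

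The Statistical analysis section compares the arms through means: an independent-samples t test, a repeated-measures analysis of variance with a group-by-time interaction, and linear regression with GEE for changes in activity and weight. Categorical tools appear in two places. Cross tabulation is for associations between response and explanatory factors in aggregated data. Logistic regression is named, alongside linear regression, for "determinants of change within the exercise group and the pooled groups".

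On numbers, the Setting and randomization section says: "These will be randomly allocated into an intervention (n = 640) and control group (n = 640) using computer-generated random numbers". It expects 447 per group at the end after 30% dropout.

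**The concern.** A power statement belongs to one endpoint and one test. Here the endpoint that was sized (inactive or not) differs from the endpoint named as primary (change in time at several intensities), and the comparisons written out for the arms are of means. The 80% has therefore been calculated for something other than the comparison that the article presents as primary.

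Three things are at stake. First, a null t test on activity time could not be read as the result of a trial with 80% power, because no power for that test has been worked out. Second, the stated aim of one third fewer inactive men has no cut-off in the article, so a later test of it would depend on a definition that the article does not fix. Third, with a continuous and a binary version of the same construct both available, the article does not settle which result decides the trial.

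**Working it through.** **Inputs from the protocol article.** p1 = 27.6% and p2 = 18.5% inactive, 80% power, 5% significance, multiplier 7.9 (Sample size); 640 randomised and 447 expected at the end per group (Setting and randomization). Not given: an SD or a target difference for activity time.

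**1. Reproduce the stated figure.**
- p1(100 − p1) = 27.6 × 72.4 = 1998.24
- p2(100 − p2) = 18.5 × 81.5 = 1507.75
- (p1 − p2)² = 9.1² = 82.81
- n = (1998.24 + 1507.75) / 82.81 × 7.9 = 334.5, so 335 per group

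The multiplier 7.9 is the rounded two-sided 5%, 80% power value (1.960 + 0.842)² = 7.849. With 7.849 the formula gives 332.3; the pooled-variance version gives 336. The arithmetic is sound for its own endpoint.

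**2. Power for that binary contrast.** Pooled-variance formula on the proportion scale: power = Φ{[0.091√n − 1.960√(2p̄q̄)] / √(p1q1 + p2q2)}, with p̄ = 0.2305.
- n = 335: 80.0%
- n = 447: 89.9%

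**3. What the same numbers give for a difference in means.** Detectable standardised difference at 80% power = 2.8016 × √(2/n).
- n = 335: 2.8016 × 0.0773 = 0.216
- n = 447: 2.8016 × 0.0669 = 0.187

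Because the article gives no SD or target difference, the standardised difference d below is an assumed range (two-sided 5%, normal approximation).

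| Assumed d | n per group for 80% | Power at 335 | Power at 447 |
|---|---|---|---|
| 0.10 | 1570 | 25% | 32% |
| 0.15 | 698 | 49% | 61% |
| 0.20 | 393 | 73% | 85% |
| 0.25 | 252 | 90% | 96% |
| 0.30 | 175 | 97% | 99% |

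Nothing in the article places the expected effect within this range.

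**4. A bridge between the two scales.** Suppose activity is roughly normal and the intervention shifts every man equally. Moving from 27.6% to 18.5% below a fixed cut-off is then a shift of z(0.276) − z(0.185) in absolute value, about 0.30 SD. That corresponds to about 97% power at 335 per group. If only the inactive men changed, the mean shift would be smaller. The article states neither assumption.

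**5. Source of the 27.6%.** 212 / 0.276 = 768, close to the 770 questionnaire responses reported for 2009 under Outcome measures. This suggests, without proving it, that the rate is self-reported, whereas daily activity in the trial is to be followed by a wrist monitor. If so, the sizing endpoint and the monitor outcome differ in instrument as well as in scale.

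**The case against.** The best defence has four parts.

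- **The source is a condensed article and the SAP is not shown.** Naming a test for a binary outcome is commonly left to the SAP. The article does name cross tabulation and logistic regression, the latter in pooled groups where arm could be an explanatory variable. This stands in part. A reader might infer that the powered aim will go untested, but the text does not support that: a between-arm test of the proportion is not explicitly stated, which is not the same as ruled out. The defence does not remove the mismatch, because no SAP can make the 80% in the Sample size section apply to the different outcome named at the start of that section.
- **The main outcome is worded broadly enough to contain a proportion inactive.** That is fair as far as the construct goes. But the Sample size section itself specifies a change in time, and the proportion is not named as an outcome.
- **No shortfall is shown.** This stands. The expected 447 per group exceed 335, give about 90% power for the binary contrast, and can detect a small standardised difference. Under the uniform-shift assumption the binary sizing is conservative for the t test.
- **Recruitment does not depend on the 335.** All eligible men at the call-ups are approached and about 1280 are expected. True, so the fault lies in the stated power and in which endpoint decides the trial, not in how many men are enrolled.

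A reader might also infer that the second hypothesis has no planned test. That goes too far: it covers self-determined and measured health, and change in weight is to be modelled. What can be said is narrower: no between-arm test of the overweight or obese proportion is explicitly stated.

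**Conclusion.** The concern holds as a mismatch within the article. The 335 per group is right for 27.6% versus 18.5% inactive, and the 80% belongs to that contrast. It does not belong to the stated primary outcome, change in activity time, or to the comparisons of means written out for the arms.

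Power for the stated primary outcome is unknown. Over an assumed standardised difference of 0.10 to 0.30 it runs from 25% to 97% at 335 per group and from 32% to 99% at 447. It would be wrong to conclude from this that the trial is underpowered: 80% is reached from about 0.19 SD with the expected completers, and an equal shift of a normal distribution that produced the planned fall would be about 0.30 SD. These figures rest on two-sided 5% testing, a normal approximation, a single continuous outcome, and the article's own dropout estimate.

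**What to change.** Make the Sample size, outcome and Statistical analysis sections agree on one primary endpoint and one test. Either of two routes will do.

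- **(a) Binary.** Name the proportion inactive at 6 months as the primary outcome, with its cut-off and instrument fixed in advance, and state a between-arm test adjusted for baseline inactivity. The present calculation then stands: 80% power at 335 per group and about 90% at the expected 447.
- **(b) Continuous.** Keep one continuous activity-time outcome and replace the power statement with the detectable difference: about 0.22 SD at 335 per group and 0.19 SD at 447, converted to minutes per day with the sponsor's own SD.

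Under either route, state how the overweight or obese proportion will be compared between arms, since it is the named secondary outcome.

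The cost is rewording and one recalculation. Route (b) may yield a less favourable figure: if the smallest difference of interest were 0.15 SD, 80% power would need 698 per group, more than the 640 to be randomised. Reporting what the planned sample can detect needs no added participants.
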